## Abstract

**Background:**

Schizophrenia is a severe mental illness with a significant disease, economic and social burden. Persecutory delusions (beliefs that one will be harmed or mistreated) are a common symptom of schizophrenia with associated high levels of depression. International clinical guidelines recommend individual cognitive behaviour therapy for schizophrenia, but there are currently no group psychological therapies recommended in NICE guidelines. We conducted a pilot randomised controlled trial, comparing group mindfulness therapy (GMT) to treatment as usual (TAU) for people with schizophrenia and persecutory delusions where we demonstrated feasibility and acceptability. It is now timely to progress to conduct a definitive randomised controlled trial (RCT).

**Methods:**

A parallel group RCT with single blind assessment comparing GMT + TAU (intervention condition) with TAU alone (control condition). The PHQ-9 and additional patient-reported psychometric measures will be collected at three time points: at baseline (prior to randomisation), end of therapy (approx 4 months post randomisation), and follow up (approx 8 months post-randomisation). Participants will be 144 adults with a schizophrenia spectrum diagnosis with current persecutory delusions or attending an early intervention in psychosis service, recruited across 3 NHS sites (Hampshire and Isle of Wight Healthcare NHS Foundation Trust, Greater Manchester Mental Health NHS Foundation Trust, and Pennine Care NHS Foundation Trust), randomised 1:1 to intervention or control groups. The therapy will be delivered according to our published manualised protocol. We will also monitor and evaluate a range of safety indices throughout the trial, conduct mediation and moderation analyses to understand how, and for whom, the therapy is most effective and assess cost effectiveness.

**Discussion:**

If shown to be effective and cost-effective, GMT will positively impact the lives of people with schizophrenia, by providing an evidence-based group therapy. This is particularly important as there are no group psychological therapies for schizophrenia in the NICE guidelines and group therapies offer the potential for cost savings for service providers. The findings will be disseminated to a range of stakeholders, including service users/carers, academic researchers, clinicians, research participants and the general public, via academic publications, conferences, plain English summary (written and video versions) and public engagement events.

**Trial registration:**

ISRCTN: ISRCTN16318074, registered on 07/02/2025.

**Supplementary Information:**

The online version contains supplementary material available at 10.1186/s12888-025-07470-3.

## Background

Schizophrenia is a severe mental illness that affects how a person thinks, feels and behaves, and has been referred to as the “abandoned illness” [1]. Worldwide, 24 million people are currently diagnosed with schizophrenia [2], and in the UK, it is over 650,000 people (around 1% of the population) [3]. The burden of schizophrenia is substantial, with impacts including earlier mortality, multiple psychiatric comorbidities such as depression, poor social functioning and unemployment [4]. People with severe mental illness, including schizophrenia, are at risk of dying on average 15 to 20 years earlier than other people. In addition to the disease burden for individuals themselves, schizophrenia also has the highest median societal cost per patient of all mental disorders [4]. The economic cost of treating schizophrenia globally is also very high – for example, mental illness costs the UK economy in excess of £77 billion per year [5], and schizophrenia accounts for around 30% of all spending in adult mental health in the NHS [6]. In the US, the societal cost of schizophrenia was reported as US$281.6 billion in 2022 [7]. Finally, in a recent systematic review of cost-of-illness studies (*k* = 24), the annual societal cost of schizophrenia per person was US$819 in Nigeria to US$94,587 in Norway [8].

One of the most common and disabling symptoms of schizophrenia is persecutory delusions, which occur when individuals believe that other people are intentionally trying to mistreat, harm or kill them [9]. Almost half of individuals with persecutory delusions have levels of well-being in the lowest 2% of the general population [10] and depression has been shown to be high in this population and predicts the persistence of persecutory delusions [11]. Given the high social, economic and individual costs of schizophrenia, and the impact of persecutory delusions in particular, it is important to improve the range of evidence-based treatments available, including seeking new ways to help individuals suffering from this debilitating mental health condition.

One of the first line treatments for schizophrenia recommended internationally in clinical guidelines is Cognitive Behaviour Therapy for psychosis (CBTp), including, for example in England and Wales, Germany, Canada, Australia and New Zealand [6, 12–14]. CBTp typically targets individual psychotic symptoms, including delusions, voices and paranoia, and is typically delivered in an individual format. There is, however, a gap in the evidence base and in current healthcare provision, as there are currently no NICE-recommended group psychological therapies for people with schizophrenia. This is important because group therapies offer the potential (subject to full health economic analyses) for cost savings for healthcare providers.

Mindfulness-based interventions (MBIs) are increasingly being used to help people with schizophrenia and are frequently delivered in a group format [15],and the evidence base for MBIs for schizophrenia is growing [16]. Mindfulness-based approaches might be particularly helpful for people with persecutory delusions as mindfulness offers the opportunity to ease distress without focussing specifically on the content of persecutory beliefs [17, 18]. A recent meta-analysis summarising the effects of group mindfulness therapy for people with schizophrenia compared with treatment as usual (*k* = 4 studies), reports an overall medium effect size (Hedge’s g = 0.46) on symptom reduction [19], but the review also concluded that there is currently no data or evidence for people with schizophrenia who experience persecutory delusions. The overall range of effect sizes reported in a recent summary of 10 published meta-analyses was 0.45–0.86, with small effects reported in three reviews, medium effects in six reviews and large effects in one review [16]. In recognition of the absence of evidence of MBIs specifically for people with persecutory delusions, and the importance of addressing this evidence gap, we conducted a pilot RCT, comparing group mindfulness alongside treatment as usual with treatment as usual alone for people with schizophrenia and persecutory delusions [20]. In our pilot trial (*n* = 27), we demonstrated feasibility and acceptability (of conducing an RCT in this patient group, of participation in a randomised controlled trial, and of the intervention itself): (1) Recruitment was completed within the pre-set timeframe; (2) 96% of participants were retained in the study (only 1 person dropped out from the treatment as usual only arm); (3) All participants allocated to receive group mindfulness therapy completed it, demonstrating acceptability of the intervention; (4) 100% adherence to the therapy protocol was achieved by all trial therapists; (5) We were able to show a signal of effect on the primary outcome (Cohen's d = 0.2); and (6) 64% who received the therapy showed a clinically significant reduction in depression symptoms. Given the success of the pilot, we have now progressed to a definitive trial to evaluate the clinical and cost effectiveness of GMT for people with schizophrenia and persecutory delusions.

As well as understanding the beneficial effects of any intervention, it is also important to evaluate any potential harmful effects. The importance of understanding any potential harmful effects of mindfulness is a current live issue in the field [21]. We recently published international guidelines for operationalising and monitoring harm in randomised controlled trials of mindfulness therapies for people with schizophrenia [22]. Using these guidelines, this current trial will evaluate safety indices in a definitive clinical trial of mindfulness for schizophrenia.

The overall aim of the study is to assess the effectiveness and cost effectiveness of GMT for people with schizophrenia and persecutory delusions. The study has the following objectives: (1) assess the effectiveness of GMT by conducting a definitive RCT comparing GMT + TAU vs TAU (TAU was chosen as the comparator as this is the first definitive trial of group mindfulness for people with persecutory delusions, and therefore TAU was considered the most appropriate control condition); (2) conduct a full health economic evaluation to determine the cost effectiveness of GMT; (3) assess adherence to the therapy protocol; (4) evaluate how GMT works and for whom the therapy is most effective; (5) undertake a full evaluation of safety indices in a definitive RCT of GMT.

Primary hypothesis: Compared with TAU, GMT + TAU will result in a significant reduction in depression immediately after the intervention (4 months post randomisation).

Secondary hypothesis 1: Compared with TAU, GMT + TAU will result in a significant reduction in depression at follow up (8 months post randomisation).

Secondary hypothesis 2: Compared with TAU, GMT + TAU will result in greater progress towards recovery, will reduce loneliness and will increase forgiveness, both after the intervention (4 months post randomisation), and effects will be maintained at follow up (8 months post randomisation).

Exploratory hypothesis: Compared to TAU, TAU + GMT will improve mindfulness and anxiety, which will mediate clinical outcomes. We will test potential moderators of effects, including clinical variables (illness duration, baseline symptom severity) and demographics (age, gender) to identify patients who may benefit more or less from GMT.

Exploratory research question: Will there be a difference in safety indices (number of serious adverse events and adverse events, drop out, hospital admissions, symptom deterioration) between TAU and GMT + TAU groups?

## Methods/design

### Study design

The design is a multi-centre, parallel group definitive randomised controlled trial with single blind assessment comparing GMT + TAU (intervention condition) with TAU alone (control condition). TAU will be measured and remain as usual in both groups. Assessments will be carried out at baseline, post therapy (4 months post randomisation) and follow up (8 months post randomisation) by study research assistants. This trial is registered at ISRCTN (ISRCTN16318074) and complies with the World Health Organization Trial Registration Data Set. Any changes or modifications to the study protocol (e.g., adding questionnaires, altering study procedures) will be formally submitted to the HRA for approval. The study may be subject to an audit at any time either by Queen Mary University of London Barts Clinical Trials Unit, the study sponsor (University of Southampton) or the Health Research Authority. This study is designed as a randomised controlled trial and will be reported in accordance with the CONSORT (Consolidated Standards of Reporting Trials) 2010 guidelines. The trial protocol, at the time of submission, is Version 6 (17.12.2024). The trial is funded by the National Institute for Health Research (NIHR), Research for Patient Benefit Programme (NIHR206786).

### Sample size

To determine a clinically significant difference between conditions at post treatment of 5 points on our primary outcome depression (consistent with pilot data), with 90% power and a significance level of 0.05, would require 120 evaluable participants. Consistent with the pilot data, the calculation assumes a standard deviation of 14 in depression, and a correlation between pre- and post- depression scores of 0.8. To allow for attrition of up to 15% (based on average attrition reported in the literature), we will aim to recruit 144 participants.

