### Randomisation

Randomisation will be managed by Queen Mary University of London Barts Clinical Trials Unit (BCTU). Participants will be randomised 1:1 to either the intervention group (mindfulness therapy + TAU) or control group (TAU alone). Randomisation will be stratified by NHS site, sex and cohort, using a minimisation algorithm incorporating a random element to ensure balance across minimisation factors and concealment of the randomisation allocation. Unblinded research personnel at each site will be informed of the randomisation allocation by the statistician at BCTU and will inform the patient of their allocation. The trial team research staff involved in data capture will remain blinded to the treatment allocation. Eligibility and consent will be verified before each patient is randomised.

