#### Clinical outcomes

Primary Outcome: Depression measured using the Patient Health Questionnaire 9 (PHQ-9). This is a 9-item measure of depression, with excellent internal consistency (α = 0.83), and is commonly used in routine clinical practice [24].Justification for primary outcome: Depression was identified as the primary outcome for the trial with the following justification: 1. Depression is associated with persecutory delusions, is highly comorbid in people with schizophrenia and has been shown to predict persecutory delusion persistence in a longitudinal study [11]; 2. Depression has been identified by experts in the field as one of the most important clinical outcomes for this client group when evaluating psychological therapies; 3. Depression was recommended as the primary outcome by our PPIEP group and was the primary outcome in our pilot trial.

We will also measure the following clinical outcomes:

Severity of psychotic symptoms, including delusions and voices, will be measured using the Psychotic Symptoms Rating Scales (PSYRATS) [25].

Recovery will be measured using the Recovery Assessment Scale (RAS). This is a 24-item measure of personal recovery, with excellent internal consistency (α = 0.92). It is one of the most widely used measures of personal recovery [26].

Forgiveness will be measured using the 10-item Trait Forgivingness Scale, which has excellent internal consistency (α = 0.92) and loneliness will be measured using the 3-item UCLA Loneliness Scale which has good internal consistency (α = 0.81) [27].

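### The sample size uses an SD of 14, which the PHQ-9 cannot have on its 0–27 range, so the stated 90% power for 5 points is not established for the primary outcome

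*Protocol article*

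**What the plan says.** The Sample size section of the protocol article sets the target as a "clinically significant difference between conditions at post treatment of 5 points on our primary outcome depression (consistent with pilot data". The stated power is 90% and the significance level 0.05. The section adds that "the calculation assumes a standard deviation of 14 in depression" and, as a further assumption, "a correlation between pre- and post- depression scores of 0.8", describes these two values as in line with the pilot, and concludes that this "would require 120 evaluable participants". On attrition it says: "To allow for attrition of up to 15% (based on average attrition reported in the literature), we will aim to recruit 144 participants". Allocation is 1:1 (Randomisation).

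The Clinical outcomes section identifies the outcome: "Primary Outcome: Depression measured using the Patient Health Questionnaire 9 (PHQ-9". It describes a 9-item measure and says that depression was also the pilot's primary outcome, but does not name the pilot's depression scale. No other depression scale appears in the article. The Background gives the pilot size as 27 and the pilot effect on its primary outcome as Cohen's d = 0.2.

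**The concern.** The SD is the input that, with the target difference and the correlation, determines the number of participants. An SD of 14 is too large for a scale that runs from 0 to 27. It is not a cautious planning value but one that the named instrument cannot produce at the size of the pilot or of the trial.

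If 14 was carried over from a wider depression scale, the 5-point difference and the correlation of 0.8 may have come with it. The 5 points would then not be a clinically significant difference on the PHQ-9, and the correlation would be untested for the PHQ-9. What is at stake is the only stated justification for the size of a trial that calls itself definitive: a reader cannot tell what power it has for what difference on its own primary outcome.

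**Working it through.** **Inputs.** From Sample size: difference 5, SD 14, correlation r = 0.8, power 0.90, alpha 0.05 (sidedness not stated; two-sided taken), 120 evaluable. From Randomisation: 1:1, so 60 per arm. From Background: pilot n = 27, pilot d = 0.2. Assumption: PHQ-9 total 0–27 (9 items scored 0–3). Power figures use the normal approximation unless noted.

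**1. The plan's own figure.** For a baseline-adjusted comparison of two means:

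- residual SD = 14 × √(1 − 0.8²) = 14 × 0.6 = 8.4
- n per arm = 2 × (1.960 + 1.282)² × 8.4² / 5² = 59.3, so 60 per arm and 120 in total
- power with 60 per arm = 90.3%

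The 120 reproduces. A one-sided test (98), a change-score analysis (132) and an unadjusted comparison (330) do not give it. The attrition step also holds: 120/0.85 = 141.2, and 144 covers it.

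**2. The largest SD that the scale allows.** A variable confined to a range R has an SD of at most R/2, here 27/2 = 13.5, reached only with half the participants at 0 and half at 27. With the n − 1 divisor:

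- n = 27 (13 at one end, 14 at the other): √(27² × 13 × 14 / (27 × 26)) = √189 = 13.75
- n = 120: 13.56
- n = 144: 13.55

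For comparison, scores spread evenly over 0–27 have SD √((28² − 1)/12) = 8.1. A population SD of 14 needs a scale at least 28 points wide.

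**3. Comparison with the pilot effect.** 5/14 = 0.36, against the reported d = 0.2. With SD 14, d = 0.2 is 2.8 points. For 5 points to be d = 0.2, the SD would have to be 25. The pilot d may have been computed on another basis, so this is supporting evidence only.

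**4. What 120 evaluable would give on the PHQ-9.** The article gives no PHQ-9 SD, so a range is assumed. SE = SD × √(1 − r²) × √(2/60). Power for 5 points = Φ(5/SE − 1.960). Difference detectable with 90% power = 3.242 × SE. No clustering is assumed.

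| SD | r | SE | Power for 5 points | Detectable difference |
|---|---|---|---|---|
| 5 | 0.8 | 0.548 | >99.9% | 1.8 |
| 6 | 0.8 | 0.657 | >99.9% | 2.1 |
| 8 | 0.8 | 0.876 | >99.9% | 2.8 |
| 10 | 0.8 | 1.095 | 99.5% | 3.6 |
| 13.5 (ceiling) | 0.8 | 1.479 | 92% | 4.8 |
| 8 | 0.5 | 1.265 | 97.7% | 4.1 |
| 10 | 0.5 | 1.581 | 88.5% | 5.1 |

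With the t distribution the last two powers are 97.5% and 88.0%.

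**5. Power at the pilot's effect.** If the true effect were d = 0.2 in units of the unadjusted SD, with r = 0.8, then 0.2/(0.6 × √(2/60)) = 1.826 and power = Φ(1.826 − 1.960) = 45%, whatever the SD.

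**The case against.** The strongest defence is that an overstated SD errs on the safe side. At r = 0.8 every SD that the PHQ-9 can have gives at least about 92% power for 5 points, so neither recruitment nor conduct needs to change. That stands, and it is why 144 should be kept. It does not rescue the stated calculation, because the reassurance rests on r = 0.8 and on the 5 points belonging to the PHQ-9, and the article establishes neither.

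It can also be said that the 0–27 range is not printed, and that in a group of 13 or 14, about one pilot arm, a sample SD of 14.01 is arithmetically possible. The range is declared here as an assumption and follows from standard scoring of the named instrument. The exception needs half the group at 0 and half at 27, so it does not make 14 a usable planning value.

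Two stronger readings are tempting.

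- A reader might infer that a positive result would not support a clinical claim, because significance could be reached well below 5 points. That is normal in a superiority trial. With the plan's own inputs, the smallest significant observed difference is already about 1.98 × 8.4 × √(2/60) = 3.0 points. The primary hypothesis claims only a significant reduction, and the Primary outcome analysis section already promises a 95% confidence interval that can be read against 5 points.
- A reader might infer that the trial is comfortably overpowered. The figures above 99.9% keep r = 0.8, use assumed SDs of 5–8 and ignore clustering, although therapy is delivered in groups and the analysis includes random cohort effects. They say nothing about an effect as small as the pilot's d = 0.2.

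**Conclusion.** The point holds as a fault in a stated input. Given 0–27 scoring, an SD of 14 is not possible for the primary outcome at the size of the pilot or the trial, and it is the value that produces 120. The claim of 90% power for 5 points is therefore not established for the PHQ-9. That the inputs come from another scale is plausible, but the article cannot confirm it; a plain error is equally open.

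The documents do not show the trial to be underpowered for 5 points, nor that its power is ample. Without clustering and with 60 per arm, power for 5 points runs from about 88% (SD 10, r = 0.5) to above 99.9% (SD 5–8, r = 0.8) over the planning values considered. It would fall lower still if a low correlation coincided with an SD near the ceiling. The 45% at d = 0.2 concerns a different and smaller effect, and does not contradict the power for 5 points.

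**What to change.** Keep 144. In the Sample size section:

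- State which instrument the 5 points, the SD of 14 and the correlation of 0.8 come from, and confirm whether the 5-point threshold is on the PHQ-9.
- Redo the calculation with an SD from PHQ-9 data, for example the blinded pooled baseline SD of enrolled participants.
- Take the pre-post correlation from PHQ-9 data as well, or show results over a range such as 0.5 to 0.8. Baseline data alone cannot supply it.
- Restate the power for 5 points and the difference detectable with 120 evaluable, and note that clustering by therapy group would make both less favourable.
- Say how the 5 points relate to the pilot's d = 0.2.

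The cost is a recalculation and a change of wording in the protocol and the statistical analysis plan, best made before any unblinded data are seen. Recruitment does not change.

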### Randomisation

Randomisation will be managed by Queen Mary University of London Barts Clinical Trials Unit (BCTU). Participants will be randomised 1:1 to either the intervention group (mindfulness therapy + TAU) or control group (TAU alone). Randomisation will be stratified by NHS site, sex and cohort, using a minimisation algorithm incorporating a random element to ensure balance across minimisation factors and concealment of the randomisation allocation. Unblinded research personnel at each site will be informed of the randomisation allocation by the statistician at BCTU and will inform the patient of their allocation. The trial team research staff involved in data capture will remain blinded to the treatment allocation. Eligibility and consent will be verified before each patient is randomised.

### Participants and recruitment

Participants will be 144 adults, recruited across three sites – Hampshire and Isle of Wight Healthcare NHS Foundation Trust (HIoW), Greater Manchester Mental Health NHS Foundation Trust (GMMHT) and Pennine Care NHS Foundation Trust. Participants will primarily be recruited through secondary care community mental health teams (CMHTs) and Early Intervention in Psychosis teams. Recruitment is expected to be completed within 18 months of the start of the trial (March 2026).

